## Abstract

**Background:**

Despite a significant decrease in smoking prevalence over the past ten years, cigarette smoking still represents the leading cause of preventable morbidity and mortality in the United States. Moreover, smoking prevalence is significantly higher among those with low levels of education and those living at, or below, the poverty level. These groups tend to be confronted with significant barriers to utilizing more traditional smoking cessation intervention approaches. The purpose of the study, Project ACTION (Adult smoking Cessation Treatment through Innovative Outreach to Neighborhoods), is to utilize a mobile clinic model, a network of community sites (i.e., community centers and churches) and an interactive mobile messaging system to reach and deliver smoking cessation treatment to underserved, low-income communities.

**Methods/Design:**

We are using a group-randomized design, with the community site as the sampling unit, to compare the efficacy of three smoking cessation interventions: 1) Standard Care - brief advice to quit smoking, nicotine replacement therapy (NRT), and self-help materials; 2) Enhanced Care - standard care components plus a cell phone-delivered text/graphical messaging component; and 3) Intensive Care - enhanced care components plus a series of 11 cell phone-delivered proactive counseling sessions. An economic evaluation will also be performed to evaluate the relative cost effectiveness of the three treatment approaches. We will recruit 756 participants (252 participants in each of the 3 intervention groups). At the time of randomization, participants complete a baseline assessment, consisting of smoking history, socio-demographic, and psychosocial variables. Monthly cell phone assessments are conducted for 6 months-post enrollment, and a final 12-month follow-up is conducted at the original neighborhood site of enrollment. We will perform mixed-model logistic regression to compare the efficacy of the three smoking cessation intervention treatment groups.

**Discussion:**

It is hypothesized that the intensive care approach will most successfully address the needs of the target population and result in the highest smoking cessation rates. In addition to increasing cessation rates, the intervention offers several features (including neighborhood outreach and use of mHealth technology) that are likely to reduce treatment barriers while enhancing participant engagement and retention to treatment.

**Trial registration:**

This randomized controlled trial is registered with clinicaltrials.gov registration number NCT00948129.

## Background

Cigarette smoking remains the largest preventable cause of death in the United States (US), accounting for an estimated 443,000 premature deaths per year [1]. It is well-documented that cardiovascular disease (29%), respiratory disease (23%), lung cancer (28%), cancers other than lung (11%), secondhand smoke exposure (11%), and other diseases (<1%) account for all smoking-related deaths [1]. The US is a global leader in tobacco control efforts, and trends indicate that smoking prevalence has decreased over the past several decades. However, pronounced health disparities still exist in access to tobacco control resources and smoking cessation programs, resulting in fewer economically disadvantaged individuals successfully quitting smoking as compared with middle- and high-income individuals [2]. Given the adverse health outcomes associated with smoking and data indicating that fewer economically disadvantaged individuals access and utilize smoking cessation services, identifying effective practices to address tobacco-related disparities are critical.

In addition to unequal access to smoking cessation services, it is well-established that the tobacco industry aggressively markets its products to members of racial/ethnic minority groups, economically disadvantaged individuals, and urban residents [3]. These groups tend to be confronted with significant barriers to utilizing traditional smoking cessation intervention approaches. Despite striking tobacco-related disparities among disadvantaged populations, few studies targeting low-income smokers have incorporated racial/ethnic minorities into the sample [4-7]. Additionally, few interventions exist to increase the range of smoking cessation services to individuals who lack access to transportation, have limited or no medical insurance, and typically do not utilize traditional health care facilities. Hence, employing innovative strategies to increase accessibility, availability, and affordability of smoking cessation services particularly among disadvantaged populations is a national public health priority [8,9].

The overarching goal of this National Cancer Institute R01-funded study (R01CA141628) is to deliver and evaluate a novel smoking cessation program targeted to low-income uninsured and underinsured individuals. “Delivering” in the context of this proposal means taking the program directly to neighborhoods where the target audience dwells. By utilizing a mobile clinic model and a network of community sites, we increase the range of cancer prevention services for individuals with limited transportation abilities and limited or no medical insurance and are therefore unlikely to use traditional health care facilities. The specific aims of the study are to: 1) compare the efficacy of three smoking cessation interventions targeting community based low-income uninsured and underinsured individuals in a group-randomized trial; 2) evaluate the role of quit motivation, nicotine withdrawal, risk perception, self-efficacy, social support, and negative affect as potential mediators of smoking abstinence; and 3) evaluate the cost-effectiveness of the three treatment conditions.

### Addressing smoking-related disparities through innovative approaches

Income and education level are among the strongest predictors of both smoking prevalence and successful cessation [10]. Comparisons of smoking prevalence data over 25 years reveal a widening gap between those at the lowest and highest income levels [11]. Recent national estimates indicate that the prevalence of smoking is highest among those individuals with less than a high school education (28.4%), those with no health insurance (28.6%), those living below the federal poverty level (27.7%), and those between the ages of 18–24 (23.8%) [12]. Furthermore, research suggests that compared to higher-SES smokers, low-income smokers have limited resources for quitting smoking and are less likely to receive assistance through the health care system [2]. Therefore, it is critically important to expand the reach of evidenced-based smoking cessation and treatment resources to population subsets with low levels of education and income.

Mobile health clinics offer a promising model for providing care to underserved populations with limited access to traditional health care services. These clinics have provided the following outreach services: acute and chronic care treatment, immunizations, dental exams, post-disaster care, prenatal care, screenings for mental health, cervical and breast cancer screenings, hearing tests, and nutrition counseling [13-21]. Mobile clinics are gaining popularity, but there are few data on outcomes beyond utilization rates. Results of a case–control study examining outcomes for prenatal care among uninsured immigrants indicated that patients using the mobile clinic received prenatal care significantly earlier than participants using prenatal care from a stationary clinic. Prenatal care on the mobile clinic was compared to stationary clinics and similar positive outcomes were found (e.g., gestational age at delivery, birth weight) [22]. Post-test knowledge and skills for 777 participants were significantly increased after a breast cancer screening and awareness effort delivered by a mobile clinic [23]. Although we identified no literature on using mobile clinics to provide smoking cessation services, the evidence from other health conditions suggests that a mobile clinic approach has great potential. A clear need exists to test the efficacy, utilization, and cost-effectiveness of using a mobile clinic to promote access to smoking cessation services among low-income smokers.

As cell phone use has become more widespread [24], efforts to use mobile technology for health-related interventions (mHealth) have greatly increased. For many economically disadvantaged individuals, a cell phone may be the only technological device with basic computing capabilities. For example, preliminary results from the Centers for Disease Control and Prevention (CDC) National Health Interview Survey (NHIS) indicate that adults living in poverty (30.9%) or near poverty (23.8%) were more likely to be living in households with only wireless telephones than higher income adults (16.0%) [25]. Wireless-only adults were also more likely to be current smokers (30.6%) than were adults living in landline households (18.0%); wireless-only users were additionally more likely to be uninsured (28.7%) compared to those residing in landline households (13.7%). Finally, compared with adults living in households with landlines, wireless-only adults were more likely to have experienced financial barriers to obtaining needed health care, and they were less likely to have access to routine medical care [25].

Several recent smoking cessation studies utilizing cell phones and text messaging have shown feasible and promising results [26-30]. Studies in other areas including alcohol prevention, diabetes education, sexual health, diet and physical activity have also shown promising results [31-35]. Findings from the Pew Research survey indicate that 17% of cell phone owners have used their phones to find medical information, and 9% have downloaded an application to help track or manage their health [24]. Hence, widespread cell phone use offers public health experts the opportunity to disseminate programs and interventions to populations by capitalizing on their extant adaptation and utilization of mobile technology as a vehicle to improve health outcomes.

## Methods/Design

### Smoking cessation intervention approaches

Project ACTION (Adult smoking Cessation Treatment through Innovative Outreach to Neighborhoods) is currently underway. In this study, we are employing a group-randomized design, with the neighborhood site as the sampling unit, to compare the efficacy of three smoking cessation interventions: 1) Standard Care (SC) - brief advice to quit smoking, nicotine replacement therapy (NRT), and self-help materials; 2) Enhanced Care (EC) - standard care components plus a cell phone-delivered text/graphical messaging component; and 3) Intensive Care (IC) - enhanced care components plus a series of 11 cell phone-delivered proactive counseling sessions. We have taken an expanded approach in the design of these interventions, which allows us to assess the benefit of adding novel components to a well-recognized standard care treatment approach. An important contribution of the current study is the assessment of these interventions in the context of a mobile smoking cessation clinic, which targets underserved smokers in their own communities.

### Participants

The University of Texas MD Anderson Cancer Center Institutional Review Board approved the study. To be eligible for the study, participants must be 18 years of age or older; have smoked at least 100 cigarettes; be English or Spanish speaking; smoke at least 5 cigarettes per day, on average; and be willing to set a quit smoking date within a week from the date of enrollment. Exclusion criteria are as follows: a positive history of a medical condition that precludes use of the nicotine patch; current use of NRT or other smoking cessation medications (e.g., Chantix or Zyban); current enrollment in another smoking cessation program; and currently pregnant or breastfeeding.

### Procedures

#### Recruitment

Participants are recruited from various neighborhood sites (i.e., community centers and churches) located throughout the large metropolitan area of Houston, Texas. During participant recruitment at each of the neighborhood sites, the research staff is available to explain the smoking cessation study to potential participants and to answer questions. The research staff then individually obtains informed consent from those who are eligible and interested in enrolling in the smoking cessation trial. At the time of enrollment, participants complete a baseline assessment, consisting of smoking history, socio-demographic, psychosocial, and health literacy questions. Monthly cell phone assessments are conducted for 6 months post-study enrollment, and a final 12-month follow-up assessment is conducted in-person at the original neighborhood site of enrollment.

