#### Cell phone delivered text messages and picture messages

Introducing cessation treatment within the neighborhood sites through a mobile clinic is an important step. However, the intensity of the treatment that can feasibly be provided in a single mobile clinic visit is limited. Additionally, time constraints associated with the neighborhood site visit will also limit the provision of support, teaching of coping skills, and general relapse prevention assistance. The literature indicates that most individuals who quit smoking relapse within the first week of abstinence [41], and that increasing treatment intensity decreases relapse rates [36]. Therefore, when time limitations are combined with the infrequency of site visits, the need for an extension of treatment outside of a single mobile clinic visit is clear. We address these issues by providing an interactive text and picture messaging intervention to participants in the EC and IC groups.

Participants randomized to the interactive text messaging groups (EC & IC) receive a series of text messages scheduled to begin shortly prior to their scheduled quit date, and continuing for a 3-month period. In the first week of treatment, participants receive 5 messages per day. The frequency tapers off to one message per day by week 4, and continues at this frequency until week 12. The text and picture messages are received by the participant on the cell phone provided to them by the project research staff.

The messages are designed to increase cigarette smoking and health knowledge, maintain/increase quit motivation, promote coping skills use, increase NRT compliance, increase social support, and enhance self-efficacy to quit smoking. The content of the messages is designed to fit into one of four different categories: 1) problem solving/coping skills; 2) knowledge/risk perception; 3) increasing and maintaining quit motivation; and 4) increasing social support. Additionally, to address the specific needs of each participant, the text messages are tailored on four levels: 1) smoking status; 2) disease history; 3) concern of future disease; and 4) preferred coping skills. These characteristics are ascertained through baseline data collection. Text messaging content is primarily drawn from cognitive-behavioral and Motivational Interviewing (MI) techniques.

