### Power considerations

The study uses a group-randomized design with repeated observations at baseline, monthly for the first 6 months post intervention, and at 12 months post intervention. A total of 126 neighborhood sites will be stratified according to type (community center vs. church) and ethnic composition, and randomly assigned from within strata to one of three treatment conditions: SC, EC, or IC conditions. This will yield 42 centers per condition. Sample size was estimated using parameters obtained from the published literature and from our own research [1,74]. The total sample size will be 756 (252 participants in each of the 3 treatment conditions) which allows for 95% power to detect a net difference of 11% or larger between the treatment groups and accounts for multiple comparisons for the three pairwise comparisons.

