**Figure 2 F2:**
[figure not shown]
CONSORT diagram: Project ACTION.

**Table 2 T2:** Demographic characteristics of sample

**Characteristic**	**Standard Care (n=114)**		**Enhanced Care (n=46)**		**Intensive Care (n=67)**		**Total (n=227)**	
Mean age in years (SD)	46.9	(12.7)	48.3	(12.7)	47.4	(11.7)	47.3	(12.3)
Male, n (%)	53	(46.5)	23	(50.0)	26	(38.8)	102	(44.9)
Married/living with significant other, n (%)	28	(24.6)	22	(47.8)	20	(29.9)	70	(30.8)
Race/ethnicity, n (%)								
White	7	(6.1)	4	(8.7)	9	(13.4)	20	(8.8)
African American/Black	96	(84.2)	33	(71.7)	49	(73.1)	178	(78.4)
Hispanic/Latino	8	(7.0)	5	(10.9)	7	(10.5)	20	(8.8)
Other	3	(2.6)	4	(8.7)	2	(3.0)	9	(4.0)
Mean years of formal education (SD)	11.3	(3.0)	11.9	(2.8)	11.4	(3.3)	11.4	(3.1)
Education level, n (%)								
Less than high school	30	(26.3)	11	(23.9)	13	(19.4)	54	(23.8)
High school or equivalent	52	(45.6)	20	(43.5)	29	(43.3)	101	(44.5)
More than high school	32	(28.1)	15	(32.6)	25	(37.3)	72	(31.7)
Current work status, n (%)								
Working full or part time	56	(49.1)	21	(45.7)	31	(46.3)	108	(47.6)
Not working due to health	11	(9.7)	8	(17.4)	13	(19.4)	32	(14.1)
Cannot find work	30	(26.3)	12	(26.1)	11	(16.4)	53	(23.4)
Not working for other reasons	17	(14.9)	5	(10.9)	12	(17.9)	34	(15.0)
Annual household income <$10,000, n (%)	55	(48.3)	13	(28.3)	38	(56.7)	106	(46.7)

Although all three interventions will be made easily accessible to the target audience and are likely to have an impact, we believe that the IC intervention will most successfully address the needs of low-income smokers. First, the IC program will be personalized and equipped with an intensive, extended counseling and support module provided over the cell phone. Second, the program will combine three intervention components featuring high potential for maintaining support and motivation to quit and prevent relapse. Third, the IC intervention makes use of cell phone technology – an approach that has demonstrated efficacy and feasibility among low-income smokers (i.e., underserved HIV-positive smokers) in previous research conducted by the investigative team [74]. However, we recognize that the IC approach is also expected to be the most expensive; therefore, we will perform an economic evaluation to determine the cost effectiveness of the three treatment approaches.

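### Arms are assigned by site, and study staff appear to recruit individuals after that, so enrolment can depend on the arm; the wording about participants being randomised offers no protection

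*Protocol article*

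**What the plan says.** **Unit of allocation.** In the section on intervention approaches, "we are employing a group-randomized design, with the neighborhood site as the sampling unit". Power considerations adds that 126 sites are stratified by site type and ethnic composition and then "randomly assigned from within strata to one of three treatment conditions: SC, EC, or IC conditions", and states: "This will yield 42 centers per condition".

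**Recruitment.** Under Recruitment, research staff at each site explain the study and answer questions, after which "The research staff then individually obtains informed consent from those who are eligible and interested in enrolling in the smoking cessation trial". That section places the baseline assessment at enrolment.

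**Wording that points to individual randomisation.** The abstract says: "At the time of randomization, participants complete a baseline assessment". The section on text and picture messages says: "Participants randomized to the interactive text messaging groups (EC & IC) receive a series of text messages".

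**Analysis.** Data analysis plans a logistic mixed model for 7-day abstinence at 12 months, with site as a random effect nested in condition, treatment as a fixed effect, and covariates that the article does not list.

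**The concern.** Randomising sites makes the sites comparable in expectation. It makes the enrolled people comparable only if enrolment at a site does not depend on that site's arm. When the arm is known to the recruiter or the prospective participant, the recruiter may present the study differently, and people may accept or decline according to what is on offer.

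The packages differ in ways people would notice. Enhanced care adds messaging and a hotline, and intensive care adds 11 counselling calls. Eligibility also requires willingness to set a quit date within a week, a motivational criterion that could respond to the support offered.

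What is at stake is the primary comparison. A difference in motivation or circumstances between those who join under each arm would enter the EC against SC and IC against EC contrasts as if it were a treatment effect.

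**Working it through.** **1. Order of events.** The article gives three facts.
- Power considerations assigns sites within strata defined by site characteristics. This needs no enrolled participants.
- Recruitment has staff consent people one at a time at the site.
- The text-messaging section describes treatment introduced in a single mobile clinic visit.

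Many people enrol per site: 227 / 14 = 16.2 so far, against a planned 756 / 126 = 6. All of them share one arm. Even if a site were randomised only when its first participant completed baseline, as a literal reading of the abstract might allow, later enrollees at that site would join after its arm was set. The exception is a site where everyone consents before anyone is told the arm, and the article describes no such step.

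**2. Conflict in wording.** The abstract ties the participant's baseline to randomisation, while Recruitment ties the same assessment to enrolment. The text-messaging section has participants randomised, while the design and power sections have sites randomised. Under site allocation a participant has no randomisation of their own, so the abstract's phrase gives no individual-level protection.

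**3. What the model does.** The site random effect represents correlation among people from one site. Arm-dependent enrolment shifts the average prognosis of all sites in an arm in the same direction. That shift is confounded with the fixed treatment effect and stays in it.

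**4. Whether Table 2 shows selection.** Pearson chi-square across three arms (2 df), ignoring clustering:
- Married or with partner: 28/114 (24.6%), 22/46 (47.8%), 20/67 (29.9%); chi-square 8.36, p = 0.015.
- Income below $10,000: 55/114 (48.2%), 13/46 (28.3%), 38/67 (56.7%); chi-square 9.09, p = 0.011.

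The article gives no intracluster correlation (ICC), so a range is assumed. Design effect = 1 + (16.2 − 1) × ICC, and chi-square is divided by it:

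| Assumed ICC | Design effect | p, partner | p, income |
|---|---|---|---|
| 0.02 | 1.30 | 0.041 | 0.031 |
| 0.05 | 1.76 | 0.093 | 0.076 |
| 0.10 | 2.52 | 0.19 | 0.165 |

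These are the two most extreme of eight characteristics. The other six, also ignoring clustering, give: sex p = 0.45, race/ethnicity 0.27, education level 0.72, work status 0.39, age 0.81, years of education 0.53. Neither of the two unadjusted p-values falls below 0.05 / 8 = 0.006. The small EC group (n = 46) drives both: SC against IC gives p = 0.44 for partner status and 0.27 for income.

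The uneven enrolment (114, 46, 67; SC share 114 / 227 = 50.2%) is no clearer. In a simulation of 14 sites split 5/5/4, the largest arm reached that share with probability about 0.00, 0.03, 0.15 and 0.31 for assumed coefficients of variation of site size of 0.25, 0.5, 0.75 and 1.0. With a 7/3/4 split the probability was about 0.5 throughout (0.47 to 0.55). The shown text does not give the number of sites per arm.

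**5. What can still be protected.** 756 − 227 = 529 participants, and 126 − 14 = 112 planned sites.

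**The case against.** The strongest reply is that the article never says a site's arm is fixed or disclosed before its people are approached, nor that staff or participants know it at consent. A condensed article may leave concealment and consent scripts to the full protocol. This stands as far as it goes: a reader might infer that the article documents unconcealed recruitment, and it does not. The order is a strong inference from site-level assignment and on-site consent.

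Second, the abstract's phrase is loose, and speaking of participants as randomised is ordinary shorthand in cluster trials. Agreed: the wording correction alone is clerical. The substance is that no individual randomisation exists to fall back on.

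Third, shared inducements dilute arm-driven enrolment. Everyone receives a phone to keep, paid monthly assessments over it, free patches, advice and materials. This also stands. A reader might infer that standard care involves no phone contact. In fact it lacks messaging, hotline and counselling, but not the monthly assessment calls. Shared benefits lessen the incentive to choose by arm without removing it.

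Fourth, a reader might infer from Table 2 that selection has already happened. The documents do not support that, for the reasons in the check above.

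Finally, hiding the arm from staff who also deliver the package may not be feasible, and changing procedure now mixes two recruitment regimes. Both are fair limits. The first is why staff concealment is asked for only where feasible. The second does not justify leaving the remaining recruitment unprotected.

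**Conclusion.** The point holds as a design weakness worth correcting. Sites are randomised, individuals appear to be recruited and consented at sites whose arm is already set, and neither the participant-randomisation wording nor the site random effect protects against arm-dependent enrolment.

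This rests on two assumptions: that allocation precedes recruitment at a site for at least its later enrollees, and that the arm can become known at consent. If the full protocol already places consent and baseline before disclosure, only the wording needs repair.

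The direction and size of any bias cannot be derived from the article. What can be stated is the exposure: 529 of 756 participants (70%) remain to be enrolled. Table 2 is compatible with chance and few, unequal sites, and carries no weight in this conclusion.

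**What to change.** For the remaining sites:

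1. Use one arm-neutral script, and complete screening, consent and the baseline assessment before the participant is told the site's arm. Where feasible, release the arm to recruiting staff only after that too.
2. Keep a tally by site of people approached, eligible and refusing, so that differential uptake by arm can be seen and reported.
3. Reconcile the abstract, Recruitment and the text-messaging section to say that sites are allocated and participants are enrolled. State where enrolment and baseline fall relative to allocation and its disclosure.
4. Adjust the Aim 1 model for baseline covariates already collected and chosen for prognostic value, for example nicotine dependence (FTND) and income, which the article itself ranks among the strongest predictors of cessation. Do not choose them because they happen to be imbalanced at the interim. For the 227 already enrolled, whose recruitment cannot be repeated, this is the available safeguard, and it addresses only measured differences.

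The cost is a consent text that describes all three packages, with likely ethics review, a screening log, and arm-specific set-up moved to after baseline. The sample size need not change. If the order in step 1 is already in use, a sentence saying so settles that part.
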